## Study Setting and Period

This study will be conducted in the Dale and Wonsho districts of Sidama National Regional State, Ethiopia from 01 June – 24 July 2022. Both woredas are known for their highly dense population and coffee production. Dale district (woreda) has 10 health centers and 33 health posts. Hamlin Fistula Center, which provides care for fistula cases and pelvic organ prolapse is found in Yirga-Alem town in Dale district. Wonsho district has five health centers and 17 health posts. According to the 2021 report of Sidama Regional Health Bureau, the total population of Dale district is 254,653 and that of Wonsho district is 129,730 ([134](#_ENREF_134)). According to the Ethiopian Central Statistical Agency, the female population accounts for 49.7% of Dale woreda population and 49.2% of Wonsho population ([135](#_ENREF_135)). Dale district has 36 rural and two urban kebeles while Wonsho district has 17 rural and one urban kebeles (smallest administrative units in Ethiopia).

In 2017, Hawassa University has established its own Health and Demographic Surveillance System site in Dale and Wonsho districts of Sidama Region. The HDSS site include 10 rural kebeles and two urban kebeles. The Surveillance site is called Dale-Wonsho Health and Demographic Surveillance Site (D-W HDSS). The Map of the HDSS site is obtained from previous study (Figure 2).

[figure not shown]

Figure 2: Map of Hawassa University Health and Demographic Surveillance System Sites from Dale and Wonsho Districts ([136](#_ENREF_136)).

.

## Study Design

A community-based cross-sectional survey design will be used to determine the prevalence of pelvic organ prolapse among women in the Sidama region. In a survey study, data are collected either from the whole population or a subset of the population to answer the research question. These studies are useful to assess the burden of disease and inform the planning and allocation of resources. A survey study should be representative of the population to have valid generalization ([137](#_ENREF_137)).

## Study Population

All women who have given birth (at least once) or ≥ 18 years old, and permanent residents (≥ 6months) of the Health and Demographic Survey Site of Hawassa University will be included in this study.

**Inclusion Criteria:** Women whose household information is found in the Health and Demographic Survey of Hawassa University and who have given birth or ≥ 18 years old will be included.

**Exclusion criteria:** Women who are pregnant (confirmed or suspected), in the postpartum period (six weeks), never practiced sexual intercourse, or severely sick during the data collection period will be excluded.

## Sample Size Determination

The sample size was calculated using Open-Epi version 3.1 both for the prevalence of the POP and its associated risk factors. The sample size for the pelvic organ prolapse prevalence study was calculated based on the prevalence of pelvic organ prolapse of 56.3%, a non-response rate of 7% from previous similar study([39](#_ENREF_39)), with the assumption of a 95% confidence interval, and a design effect of 2, the final sample size is 813.

The sample size was also calculated for risk factors from a previous similar studies conducted in the northern part of Ethiopia ([39](#_ENREF_39)) by using Open-Epi version 3.1. For each variable significantly associated with POP, the sample size was calculated with the assumption of 95% confidence level, 80% power, unexposed to exposed ratio of one to one, proportion of outcomes among unexposed categories, and their respective odds ratios. Finally, a design effect of two and non-response rate of 7% were used to calculate the final sample size (Table 1).

Table 1: Sample size calculation based on risk factors of Pelvic Organ Prolapse for the study to be conducted in Sidama National Regional State, Ethiopia, 2022.

| Exposure Variables | | Confidence level | Power | % with outcome | Odds ratio | Design effect | % non-Response rate | Sample size |
| --- | --- | --- | --- | --- | --- | --- | --- | --- |
| Women age | ≤34 | 95% | 80 | 17.58 | Reference | | | |
|  | 35-44 | 95% | 80 | 49.15 | 2.21 | 2 | 7 | 659 |
|  | >45 | 95% | 80 | 29.970.1 | 3.57 | 2 | 7 | 246 |
| Parity | 0 | 95% | 80 | 11.6 | Reference | | | |
|  | 1 | 95% | 80 | 21.15 | 3.16 | 2 | 7 | 396 |
|  | 2 | 95% | 80 | 49.4 | 6.61 | 2 | 7 | 134 |
|  | 3 | 95% | 80 | 59.9 | 8.86 | 2 | 7 | 99 |
|  | 4+ | 95% | 80 | 72.5 | 11.73 | 2 | 7 | 78 |
| Hours of carrying heavy objectives | ≤1 | 95 | 80 | 25.1 | Reference | | | |
|  | 2 | 95% | 80 | 62.5 | 4.34 | 2 | 7 | 160 |
|  | 3 | 95% | 80 | 76.32 | 9 | 2 | 7 | 82 |
|  | 4+ | 95% | 80 | 64.8 | 5.1 | 2 | 7 | 134 |
| Age at last delivery | >36 | 95% | 80 | 77.1 | 2.7 | 2 | 7 | 344 |
|  | ≤36 | 95 | 80 | 51.9 | Reference | | | |

The sample size calculated for the prevalence study produced a larger sample size, 813, that will be used in this study.

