## Sampling Techniques

A complex sample survey will be used to recruit study participants. A survey sampling is a process of selecting representative samples from the population and measuring the selected samples to get evidence about population parameters ([138](#_ENREF_138)). If the selection of study participants passes through a series of stages like multilevel sampling, cluster sampling, or stratification, it is called complex sampling. The features of large survey sampling are stratification, clustering, and unequal probability sampling ([138-141](#_ENREF_138)).

The current planned study will be conducted in the Dale and Wonsho districts of the Sidama region. The two districts were selected due to the accessibility of the sampling frame from the Health and Demographic Surveillance System (DHSS) of Hawassa University. The DHSS involved a total of seven rural kebeles (Wayicho, Hida Kality, Shoye, Dagiya, Magara, Danshe sire and Gidamo); and one urban kebeles (Aposto) from Dale district, and three rural kebeles (Mamana, Bokaso and Gishire); and one urban kebele (Wonsho 01) from the Wonsho district. The list of households from these kebeles will be used for the sampling frame in the current planned study.

In this study, Hawassa University Health and Demographic Surveillance System (HDSS) site will be initially stratified into two districts (Dale and Wonsho). Then each district will be re-stratified into urban and rural kebeles. Since there are only one urban kebeles included in to the DHSS from each district, both kebeles will be selected to ensure representativeness. From rural kebeles, representative kebeles will be selected from both districts (four rural kebeles from Dale and two rural kebeles from Wonsho district) based on their selection probability. If the selected rural kebeles (clusters) are adjacent to each other, the second cluster will be replaced by the next kebele (cluster) to create a buffer zone. Finally, equal number, 101.6 approximated to 102, eligible women from each kebele (clusters) will be selected using computer-generated random numbers. This approximation will adjust the sample size to 816 to sample equal number of participants from each clusters. Therefore, this study includes four strata: Dale-Rural, Dale-Urban, Wonsho-Rural, and Wonsho-Urban; eight clusters (kebeles) and 816 eligible women (Figure 3). If there is more than one eligible woman in the selected household, one of them will be selected by the lottery method.

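### Table 1 of Paper II gives two-group totals, but they are compared with a whole-sample 813, so 80% power is not shown for age 35–44 or parity 1 at the plan's own odds ratios

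*Protocol*

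**What the plan says.** In the protocol, Paper II, Sample Size Determination, the prevalence calculation gives 813 women. The risk-factor calculations assume 95% confidence, 80% power and an "unexposed to exposed ratio of one to one, proportion of outcomes among unexposed categories, and their respective odds ratios", after which "a design effect of two and non-response rate of 7% were used to calculate the final sample size".

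Table 1 lists one total for each non-reference category. The age rows are "≤34 | 95% | 80 | 17.58 | Reference", "35-44 | 95% | 80 | 49.15 | 2.21 | 2 | 7 | 659" and ">45 | 95% | 80 | 29.970.1 | 3.57 | 2 | 7 | 246". Parity has five categories (0, 1, 2, 3, 4+), and the parity 1 row has odds ratio 3.16 and total 396. Carrying hours has four categories and age at last delivery has two.

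The section then concludes: "The sample size calculated for the prevalence study produced a larger sample size, 813, that will be used in this study".

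Under Sampling Techniques, 102 women are drawn by random numbers in each kebele, giving "eight clusters (kebeles) and 816 eligible women". There is no quota or stratification by age or parity.

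**The concern.** A 1:1 two-group total answers the question of how many women are needed in these two categories together. It becomes a requirement for the survey only after division by the share of the sample that falls in them. Women over 45 contribute nothing to 35–44 versus ≤34, and women with two or more births contribute nothing to parity 1 versus 0. Setting 659 and 396 directly beside 813 omits that step.

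Identifying risk factors is the second objective of Paper II. Its analysis section calls a variable a predictor only if the 95% interval for the adjusted odds ratio excludes 1 and P<0.05. A null result for one of these contrasts, read under an assumed 80% power, could be taken as evidence of no association when the survey had a smaller chance of detecting it.

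**Working it through.** **Inputs (Table 1 and its text).** Two-sided 5% (read from 95% confidence), 80% power, 1:1, design effect 2, non-response 7%. Age: reference 17.58%, OR 2.21. Parity: reference 11.6%, OR 3.16. Category shares are not given, so they are assumed below.

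**1. Reproduce the plan.** p1 = p0·OR / (1 − p0 + p0·OR).
- Age 35–44: p1 = 32.04%. Parity 1: p1 = 29.31%.
- The two-proportion formula with continuity correction (Fleiss) gives 153 and 92 per group.
- Totals: 2 × 153 × 2 / 0.93 = 658 (printed 659); 2 × 92 × 2 / 0.93 = 396 (printed 396).

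The other rows reproduce within about 2%. The prevalence figure is 1.96² × 0.563 × 0.437 / 0.05² = 378, and 378 × 2 / 0.93 = 813 (the 5% precision is assumed; the text does not state it). Table 1 is therefore correct as a set of two-group totals.

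**2. Whole-sample requirement with equal shares (assumption).**
- Age: 659 × 3/2 ≈ 989. Parity 1: 396 × 5/2 = 990. Both exceed 816.
- The largest of the other rows is >45: 246 × 3/2 = 369. Only the two named contrasts fail.

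**3. Power at 816 with equal shares.** Effective number = 816 × 0.93 / 2 = 379.4, so 126.5 per age category and 75.9 per parity category. Power = Φ[(d − 1.96·SE0)/SE1], with SE0 from the pooled and SE1 from the separate proportions.
- Age: d = 0.1446, SE0 = 0.0543, SE1 = 0.0535, power 76%.
- Parity 1: d = 0.1771, SE0 = 0.0655, SE1 = 0.0639, power 78%.
- With the plan's own continuity correction, replace n by (n − 1/d)²/n, that is 113.0 and 65.0. Power is 71% for both.

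To reach 80% at 816 with that correction, ≤34 and 35–44 together would have to be about 81% of the sample, or parity 0 and 1 together about 48%, in each case split nearly evenly.

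**4. Shares tied to the plan's 56.3%.** The >45 cell prints 29.970.1. It is read here as 70.1, because with 29.9 no age mix reaches 56.3%. Equal shares do not fit: (17.58 + 49.15 + 70.1)/3 = 45.6% for age and (11.6 + 21.15 + 49.4 + 59.9 + 72.5)/5 = 42.9% for parity. Let a and b be the shares of the reference and compared categories, with everyone else at the highest prevalence (the choice most favourable to the plan), so that a·p0 + b·p1 + (1 − a − b)·pmax = 0.563. Maximising power over a and b, without continuity correction:

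| Contrast | Prevalence of compared category used for shares | Alternative used for power | Best-case power |
|---|---|---|---|
| Age 35–44 | 49.15% (row) | 32.04% (OR 2.21) | 52% |
| Age 35–44 | 32.04% (OR) | 32.04% (OR 2.21) | 44% |
| Age 35–44 | 49.15% (row) | 49.15% (row) | 99% |
| Parity 1 | 21.15% (row) | 29.31% (OR 3.16) | 64% |
| Parity 1 | 29.31% (OR) | 29.31% (OR 3.16) | 67% |
| Parity 1 | 21.15% (row) | 21.15% (row) | 28% |

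The row percentages and the odds ratios are different alternatives: 49.15% against 17.58% is a crude odds ratio of 4.53, not 2.21, and 21.15% against 11.6% is 2.04, not 3.16.

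**The case against.** Several counter-arguments carry weight.

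- **The age result depends on the alternative.** With the row's own 49.15% the age contrast has ample power. This stands. The age shortfall exists only at the odds ratio of 2.21, although that is the value the plan designed on. Parity 1 falls short under either alternative.
- **The shares are not in the protocol.** This stands, and every power figure here is conditional on assumed shares. The bounds in step 4 are the weaker ones. The literature review describes the 56.3% as prolapse of at least grade two, whereas Paper II counts stage I or more. The statement of the problem also says that the source's analyses by age and number of deliveries rested on very few observations. The equal-share figures avoid those percentages but are themselves only an assumption.
- **No sentence says that 813 covers every contrast.** Correct: the text says only that the prevalence calculation gave the larger number. A reader might infer coverage of all rows at 80%. The inference is natural, but the protocol does not make the claim. What it does make is a comparison of unlike quantities.
- **Age and parity would still be found.** A reader might infer that the survey could miss them as risk factors. The documents do not support that: at equal shares the >45 row and the higher-parity rows all stay well below 813. What is weak is the step between two low categories.
- **The regression is not tied to Table 1's categories.** Also correct. Study Variables already lists age in years and number of childbirths, so a continuous or ordered term is open to the analyst and its absence is no error.

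**Conclusion.** The point holds in limited form. Table 1's arithmetic is right for two equal groups; the error is treating those totals as requirements for the whole survey. At the plan's own odds ratios, 816 women are not shown to give 80% power for age 35–44 versus ≤34 or for parity 1 versus 0, and 813 is not shown to be the largest requirement. With equal shares the shortfall is moderate: about 990 women needed and about 71% power. It is larger if the 56.3% prevalence and the category percentages all hold. It would disappear only with category shares that do not fit those same figures, or, for age alone, with the larger effect implied by 49.15%.

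A reader might also conclude that 813 is too small altogether, or that the randomised trial is affected. Neither follows. The 813 reproduces for the prevalence objective, and the trial in Papers III and IV has its own sample-size calculation.

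**What to change.** Keep 816. In Paper II, Sample Size Determination:

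1. State the expected share of women in each age and parity category and its source. The surveillance-site data may supply the age distribution.
2. Convert each Table 1 total to a whole-sample requirement using those shares, and correct the run-together >45 percentage.
3. Replace the 80% for age 35–44 and parity 1 with the achievable power at 816. Name the alternative used (odds ratio or row percentage), the shares, and whether a continuity correction applies.
4. Say that 813 was chosen for the prevalence objective, and that a non-significant result for either contrast will be reported with its interval and not read as evidence of no association.

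Modelling age and number of deliveries as continuous or ordered terms would use all respondents, but it is optional and would need a check of linearity.

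The cost is a recomputed table and a few sentences. No further women are needed; the stated power becomes less favourable for two contrasts.

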## Sampling Techniques

A complex sample survey will be used to recruit study participants. A survey sampling is a process of selecting representative samples from the population and measuring the selected samples to get evidence about population parameters ([138](#_ENREF_138)). If the selection of study participants passes through a series of stages like multilevel sampling, cluster sampling, or stratification, it is called complex sampling. The features of large survey sampling are stratification, clustering, and unequal probability sampling ([138-141](#_ENREF_138)).

The current planned study will be conducted in the Dale and Wonsho districts of the Sidama region. The two districts were selected due to the accessibility of the sampling frame from the Health and Demographic Surveillance System (DHSS) of Hawassa University. The DHSS involved a total of seven rural kebeles (Wayicho, Hida Kality, Shoye, Dagiya, Magara, Danshe sire and Gidamo); and one urban kebeles (Aposto) from Dale district, and three rural kebeles (Mamana, Bokaso and Gishire); and one urban kebele (Wonsho 01) from the Wonsho district. The list of households from these kebeles will be used for the sampling frame in the current planned study.

In this study, Hawassa University Health and Demographic Surveillance System (HDSS) site will be initially stratified into two districts (Dale and Wonsho). Then each district will be re-stratified into urban and rural kebeles. Since there are only one urban kebeles included in to the DHSS from each district, both kebeles will be selected to ensure representativeness. From rural kebeles, representative kebeles will be selected from both districts (four rural kebeles from Dale and two rural kebeles from Wonsho district) based on their selection probability. If the selected rural kebeles (clusters) are adjacent to each other, the second cluster will be replaced by the next kebele (cluster) to create a buffer zone. Finally, equal number, 101.6 approximated to 102, eligible women from each kebele (clusters) will be selected using computer-generated random numbers. This approximation will adjust the sample size to 816 to sample equal number of participants from each clusters. Therefore, this study includes four strata: Dale-Rural, Dale-Urban, Wonsho-Rural, and Wonsho-Urban; eight clusters (kebeles) and 816 eligible women (Figure 3). If there is more than one eligible woman in the selected household, one of them will be selected by the lottery method.

Dale rural (7) () kebele

816 women will be invited to a nearby health facility

Wonsho rural (3) kebele

Select 4kebeles women

Select 2 kebele

Dale Urban 1

Wonsho Urban 1

102 women selected kebeles kebele selected

408 women

102 women selected kebeles kebele selected

204 women selected eles kebele selected

Dale district 8kebeles

Wonsho district 04 kebeles

Select 1kebele women

Select 1kebele women

Dale-Wonsho Health and Demographic Survey Site

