## Data Management and Analysis

Data will be entered into Epidata version 3.1 and exported to STATA version 16 for analysis. The entered data will be cleaned and recoded before analysis. If there is any missing data, multiple imputation methods will be used to manage the missing data.

Before performing the main analysis, data will be weighted using the sample selection probability and the weighting class adjustment method to control for selection bias and non-response bias respectively ([147](#_ENREF_147), [148](#_ENREF_148)) based on the auxiliary data collected for the Demographic and Health Survey by Hawassa University.

The nature of the data and its distribution will be checked to identify any special distribution. For categorical data, its frequency will be run and checked for any unusual distribution. For continuous data, both statistical methods (mean, standard deviation, median, Skewness, and kurtosis); and graphical presentations (histogram) will be used to check its normal distribution. A mean and standard deviation will be reported for normally distributed data, while the median and interquartile ranges will be reported for non-normally distributed data.

The primary outcome in this study is the presence of anatomical pelvic organ prolapse, which is pelvic organ prolapse of stage I or more prolapse diagnosed through pelvic examination.

To identify predictors of POP, initially, data stratification will be done to identify possible confounders and effect modifiers ([149](#_ENREF_149)). Variable are considered confounding when their crude result (unadjusted odds ratio) is different from Mantel-Haenszel (M-H) (adjusted odds ratio) on stratified data ([150](#_ENREF_150)). An effect modifier is considered when the odds ratio of a variable is different across the strata.

In addition, the multicollinarity of the independent variables will be checked before the variable is fitted into multivariable logistic regression. In the multiple linear regression model, the variance inflation factor (VIF) > 1 and tolerance statistics < 0.1 show the presence of multicollinarity. The variance inflation factor (VIF) of 1-5 shows moderate multicollinarity, while VIF >5 shows high multicollinarity. In this analysis, variables with high multicollinarity will be omitted from the analysis ([151](#_ENREF_151)).

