# **COLLABORATORS**

This project needs the collaboration of different stakeholders to be effectively accomplished. Hawassa University, the home base of research teams, will review the protocol and provide ethical approval and some financial support of 60,000 Ethiopian birr (equivalent to 1,200 dollars). Most of the budget needed will be covered by the University of Minnesota, Maternal Health and the Worldwide Fistula Fund. The gloves and spatula needed to measure prolapse stage will be provided by the Ethiopian Hamlin Fistula Center. The Yirgalem Hamlin Fistula Center and selected health facilities will allow pelvic examination rooms and health professionals needed to examine study participants and provide training on PFMT (Table 3).

Table 3: Potential collaborators and their role for the study on Pelvic Organ Prolapse in Sidama Region, Ethiopia, 2022

|  | **Collaborators** | **Responsibility** |
| --- | --- | --- |
|  | Hawassa University | Provide Ethical Clearance |
|  |  | Provide study participants basic information from the database (HDSS) |
|  |  | Provide 60,000 ETB ($1200) for data collections |
|  |  | Assign senior research advisors |
|  | Sidama region health Bureau | Provide permission and support letter |
|  | Yirgalem Hamlin Fistula Center. | Provide patient pelvic examination site |
|  |  | Provide treatment for advanced-stage Prolapses |
|  |  | Assign and allow time for urogynaecologist to train and supervise the pelvic examination process. |
|  |  | Assign two trained health professionals to perform pelvic examinations. |
|  | Respective health centers | Provide patient pelvic examination site and materials |
|  |  | Assign two female Midwives/Nurses to train and counsel women on PFMT. |
|  | Health Extension workers | Remind and took patients to follow up site (health facility) |
|  |  | Counsel and convince participants to adhere to the training protocol |
|  |  | Support women to record pelvic exercises they performed |
|  | University of Minnesota | Provide financial support |

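### Paper II picks one woman per household by lottery, but neither the weighting plan nor the form carries the number of eligible women, and the unit drawn is ambiguous

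*Protocol*

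**What the plan says.** The Sampling Techniques section of Paper II describes the draw in three statements that do not fully agree.

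- The frame: "The list of households from these kebeles will be used for the sampling frame in the current planned study".
- The draw within a kebele, 102 in each of eight: "eligible women from each kebele (clusters) will be selected using computer-generated random numbers".
- The last step: "If there is more than one eligible woman in the selected household, one of them will be selected by the lottery method".

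The Paper II section on data collection tools and procedures sends interviewers to selected households to interview one eligible woman in each. Figure 3, by contrast, counts women selected per kebele and labels a step as simple random sampling.

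On weighting, the Paper II Data Management and Analysis section says "data will be weighted using the sample selection probability and the weighting class adjustment method to control for selection bias and non-response bias respectively", and then "based on the auxiliary data collected for the Demographic and Health Survey by Hawassa University". It gives no formula for the selection probability.

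The cover line of the form (Annex II, repeated in Annex III) has fields for woreda, kebele, enumeration area, code and mobile number. None of the ten parts is a household roster. The wealth section counts sleeping rooms, animals and households sharing a toilet, but no part counts eligible women.

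**The concern.** When one person is taken from each sampled household, the household stage gives every household the same chance, and the lottery then divides that chance among the eligible women. A weight that stops at the kebele and household stages gives women from multi-woman households too little influence. The correct weight needs k, the number of women who were in the lottery.

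The interviewer knows k at the door, and the form does not keep it. An analysis plan written later can specify a weight, but it cannot restore a count that was never recorded at the visit.

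Paper II's main result is a prevalence, and its Table 1 shows steep gradients by age and parity. Household composition is likely to be related to both, so it is unsafe to assume equal prevalence across household types.

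**Working it through.** **1. The plan's own figure.** Inputs from Sample Size Determination in Paper II: prevalence 56.3%, 95% confidence, design effect 2, non-response 7%. The margin d is not stated. Taking d = 0.05:

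2 × 1.96² × 0.563 × 0.437 / 0.05² = 756.1, and 756.1 / 0.93 = 813.0.

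This matches the stated 813. Margins of 4 and 6 points would give about 1,270 and 565, so 5 points is the margin implied. Then 813 / 8 = 101.6, rounded to 102, and 8 × 102 = 816.

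**2. Selection probability under each reading.**

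- Households drawn: P(woman) = P(kebele) × P(household | kebele) × 1/k. The weight needs a factor k.
- Women drawn from a list of women: a household's chance of being reached rises roughly in proportion to k, and the lottery divides by k. The two roughly cancel, so no factor is needed.

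**3. Bias if households are drawn and k is omitted.** Let a share s of households have k eligible women, with prevalence p2, and the rest have one, with prevalence p1. Other weight components are taken as equal.

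- Share of women from multi-woman households in the sample: s
- Share among all eligible women: ks / (1 − s + ks)
- Bias = [s − ks / (1 − s + ks)] × (p2 − p1)

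The protocol gives neither the distribution of k nor the prevalence gap. The ranges below are assumptions.

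| s | k | share in sample | share in population | bias, 5-point gap | bias, 15-point gap |
|---|---|---|---|---|---|
| 0.2 | 2 | 20% | 33.3% | 0.67 | 2.00 |
| 0.4 | 2 | 40% | 57.1% | 0.86 | 2.57 |
| 0.2 | 3 | 20% | 42.9% | 1.14 | 3.43 |
| 0.4 | 3 | 40% | 66.7% | 1.33 | 4.00 |

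Bias is in percentage points. Prevalence is understated if it is higher in multi-woman households and overstated if it is lower.

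**4. Can the sign be known?** Table 1 gives 17.58% with the outcome at age 34 or under and 49.15% at 35-44. The cell for the oldest group is garbled and may read 70.1%. A household pairing a woman of 34 or under with one of 35-44 averages (17.58 + 49.15) / 2 = 33.4%. Pairing her with one from the oldest group averages (17.58 + 70.1) / 2 = 43.8%. Against an assumed 50% in other households, the gaps are −16.6 and −6.2 points. With k = 2 the overstatement runs from 0.133 × 6.2 = 0.8 points (s = 0.2) to 0.171 × 16.6 = 2.9 points (s = 0.4). An opposite assumption gives an understatement of similar size.

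**5. Cost in precision of weighting by k.** Kish design effect = [(1 − s) + s·k²] / [(1 − s) + s·k]².

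- k = 2: 1.6 / 1.44 = 1.11 (s = 0.2); 2.2 / 1.96 = 1.12 (s = 0.4)
- k = 3: 2.6 / 1.96 = 1.33 (s = 0.2); 4.2 / 3.24 = 1.30 (s = 0.4)

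**The case against.** The best reply is that the weighting is tied to the surveillance database. Inclusion is limited to "Women whose household information is found in the Health and Demographic Survey of Hawassa University and who have given birth or ≥ 18 years old", and the Collaborators section has the university supply basic participant information from that database. A count of women per household may therefore be available without a new field. This stands in part. A reader might infer that the weights cannot be computed at all, or that the damage is beyond repair, and the documents support neither. They do not show what the database holds. Any such count would be approximate, because Study Population excludes women who are pregnant or suspected to be, recently delivered, never sexually active or severely ill, and these are settled at the visit.

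A second reply is that women, not households, are drawn. The random-number sentence and Figure 3 can be read that way, and the effect would then roughly cancel. This also stands as an ambiguity. It is not a full answer, because the frame is a household list and two sections speak of selected households. A reader should not take under-representation as established. It follows only if households are drawn and k is left out of the weight.

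A third reply is that a lottery sheet may exist separately, and that details of weighting belong in an analysis plan. A formula may indeed be left to that plan. What is recorded at the visit cannot, and the annexed form shows no place for it.

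**Conclusion.** The point holds as a gap in the design and in the form. The protocol does not say clearly whether households or women are drawn, does not put the within-household factor into the selection probability, and does not record the count that the factor needs.

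If households are drawn and k is omitted, the bias in prevalence is about 0.7 to 2.6 points. This assumes that 20-40% of households have two eligible women and that prevalence differs by 5 to 15 points either way. With three eligible women it is about 1.1 to 4.0 points. The yardstick is the implied 5-point margin, which is a back-calculation and not a stated target.

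A reader might infer that older women are the ones lost and that prevalence is therefore understated. The documents do not support a direction. The lottery thins every woman in a multi-woman household alike, younger co-residents included, and the Table 1 age figures can produce an overstatement instead.

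The consequence is confined to the prevalence and risk-factor estimates of Paper II. Trial participants come from this survey, but the randomised comparison in Papers III and IV is not biased by it.

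**What to change.** Three changes, made before fieldwork:

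1. In Sampling Techniques, state that households are the unit drawn within each kebele, and bring the random-number sentence and Figure 3 into line.
2. Add a field to the cover line of both language versions, *number of eligible women in this household*, filled in when the lottery is drawn.
3. In the Paper II Data Management and Analysis section, write the selection probability as kebele × household × 1/k and multiply each weight by k. No fixed cap is needed.

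The cost is one form field and somewhat more variable weights, with a Kish design effect of about 1.1 for k = 2 and about 1.3 for k = 3. If that came wholly on top of the planned design effect of 2, a 5-point margin would become about 5 × √1.12 = 5.3 points for k = 2, or 5 × √1.33 = 5.8 points for k = 3.
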